
#### 2.2.2. Description of Logistics Organization of the Study

Participants will benefit from NLP and sophrology interventions at the hospital. All measures will be conducted at the CHU Clermont-Ferrand. During the study, if a participant expresses particular psychic difficulties, support will be offered to him: appointment with the psychologist of the occupational health service of the CHU or referral to the attending physician according to his wishes.

#### 2.2.3. Biological Assessment

Each participant will perform a self-collection of saliva upon waking up, to control the circadian rhythm of biomarkers. Saliva sampling will be collected with the use of dedicated eppendorfs, at the CHU of Clermont-Ferrand. Centrifugation, aliquotage, and conservation of saliva will be achieved at the “Institut de Médecine du Travail, Faculté de Médecine, [name]”. The following biomarkers will also be measured at the “Institut de Médecine du Travail”, using ELISA kits: Cortisol [23,24,25], DHEAS [23,24,26], Leptin [27,28], Ghrelin [28,29,30,31]. The samples will be kept until the end of the study and then they will be destroyed.

### 2.3. Ethics and Dissemination

The protocol, information and consent form had received the favorable opinion of the Ethics Committee North-West IV. The study is registered in ClinicalTrials.gov under the identification number NCT05425511. Notification of the approval of the Ethics Committee was sent to the study sponsor and the competent authority (ANSM). The results of questionnaires will be coded and managed through REDCap^®^ secure web platform with pseudonymous codification. The results will be reported according to the CONSORT guidelines.

### 2.4. Eligibility Criteria

The inclusion criteria are to be an HCW or an NHCW from a healthcare institution (such as CHU of Clermont-Ferrand, other hospitals, clinics, retirement homes), between 18 and 65 years, with a stress greater than or equal to 50 on a visual analogue scale (VAS) of stress, to be able to give an informed consent to participate in research and to be affiliated with a Social Security scheme. The exclusion criteria are to have psychiatric, cardiovascular (heart failure, arrhythmia, etc.), hepatic (liver failure, etc.), renal (kidney failure, etc.), or endocrinological diseases (diabetes, etc.) judged by the investigator to be incompatible with the study because they may interfere with the measurements. Persons who are non-affiliated to a health insurance or protected persons (minors, pregnant women, breastfeeding women, guardianship, curatorship, deprived of freedoms, safeguard of justice) or persons who refuse to participate are not included.

### 2.5. Recruitment Process

The study will be first proposed to workers of the University Hospital of Clermont-Ferrand (CHU)) using the mailing list of the staff. If there are not enough volunteers, then the study will be expanded to include all healthcare professionals. Volunteers will send an email with their contact to the address [contact]. A Clinical Research Assistant will contact them back and give them a first quick explanation of the study by phone, and will send them the information letter, so they can read it prior to the inclusion visit. Investigators will undergo the inclusion visits, either physically or by teleconsultation. Investigators will explain to each volunteer, in an exhaustive, clear and adapted manner, the research procedure, the potential benefit and the adverse effects taking into account their specificity (state of health, age, profession, habits and life projects, family environment, etc.) and will answer all questions. Participants can sign the consent form either during the consultation or later after a reflection period of 8 days. In this case, or for teleconsultation, the two signed consent forms will be returned by post or internal mail to the investigator. The investigator will keep one form, and the second form with both signature (investigator and volunteer) will be given to the volunteer at the baseline measure. They will be informed of the possibility, once their consent has been given, to withdraw it at any time.

### 2.6. Outcomes

The main outcome is heart rate variability change between M1 and M3. HRV will be measured using Zephyr™ BioHarness™ BT (Zephyr Technology, Annapolis, MD, USA). The main secondary outcomes are subjective (questionnaires: perceived stress, personality and perception of work, etc.) and objective markers of stress (biomarkers of stress such as other measures of the activity of the autonomic nervous system, DHEAS, cortisol, etc.). All outcomes are presented in Table 1.

For both groups (interventional and control groups): (i) heart rate variability, skin conductance and saliva biomarkers will be assessed once by week during the intervention period (6 to 8 sophrology sessions) and once by month the rest of the time; (ii) the short questionnaire will be collected once a week during the whole protocol (1–2 min); and (iii) the long questionnaire will be assessed only 5 times: at baseline (M0), month 1 (M1), month 3 (M3), month 5 (M5), and the end of the protocol (M7).

Outcomes will be collected by a research assistant without any link with the randomization process nor the intervention. The independence is necessary to minimize contamination of the intervention group, particularly in study designs which cannot be blinded.

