## 3. Results

### 3.1. Justification of the Sample Size

This study aims to demonstrate an improved heart rate variability in the intervention group, in comparison with the control group. According to previous data [32], it seems reasonable to estimate that effect size, for the primary analysis between M1 and M3, will be around 0.5 for HRV parameters. Effect sizes are considered small between 0.20 and 0.50, moderate between 0.50 and 0.80, and high above 0.80 [33]. To highlight such clinically relevant difference, 85 participants per randomized group will be needed for a two-sided type I error at 5% (alpha level, i.e., showing a difference that does not exist), a statistical power at 90%. If the desired power level is typically 80%, we specified a higher power level of 90%, so there would be a 90% probability that we will not commit a type II error (beta-level, i.e., failing to show a real difference) [34,35]. Finally, it is proposed to include 100 patients per group to consider loss to follow-up.

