#### 3.2.1. Heart Rate Variability (HRV)

A Zephyr™ BioHarness™ BT (Zephyr Technology, Annapolis, MD, USA) will record HRV parameters. The Zephyr™ BioHarness™ BT is a heart rate transmitter belt simply positioned on the chest, with a 26 h recording time, a beat per minute within a 25–240 range, and respiratory rate within a 3–70 range. The aim will be to demonstrate that is it possible to detect anxiety using this easy to use and cheap device. Anxiety could also be detect using the respiratory rate. In addition, the Zephyr™ BioHarness™ BT will also measure the trunk’s movements with a 3-Axis accelerometer. Recommendations of the European Society of Cardiology and the North American Society (Task Force) will be followed to examine the HRV data. Time and frequency domains will be used to explore HRV. [50]. We will also apply the methodology developed by our team [51].

We will visually check the premature beats who will be automatically reject. Several element will be analyzed in time domain: R–R intervals and their standard deviation, the number of adjacent N–N differing by more than 50 ms divided by the total number of N–N inter-vals (pNN50) and the square root of the mean squared difference of successive R–R intervals (rMSSD). The pNN5 and rMSSD are related with high frequency (HF) power and therefore to parasympathetic activity. High (0.15–0.4 Hz) and low (0.04–0.15 Hz) frequency power will be examine in the spectral domain. HF is the principal efferent parasympathetic (vagal) activity to the sinus mode, LF is an indicator for both parasympathetic and sympathetic functions. The variations of thermoregulatory mechanisms, activity of the renin–angiotensin system and the function of peripheral chemoreceptors are partially reflects by very low frequency (VLF, 0.003–0.04 Hz). Normalized units (nu), corresponding to the relative value of each power component in proportion to the total power minus the VLF component, will also be used to assessed LF and HF. Thus, the best sympathetic and parasympathetic activity seems to be represented by LFnu and HFnu, respectively. The LF/HF ratio, that is, the sympathovagal balance, will also be calculated (Table 2) [52].

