
### 3.3. Data Analysis

The SO-WELL trial statistical analysis plan (and its successive versions) will be kept in the study records. The statistical analysis plan may be revised during the study, e.g., in order to take into account amendments to the protocol or any change in the conduct of the study that may have an impact on the statistical analysis plan as described in its current version.

Statistical analysis will be performed using Stata software (v16, Stata-Corp, College Station, TX, USA). According to the International Conference on Harmonization Good Clinical Practice guidelines, analyses will be conducted before the breaking of the randomization code. The primary analyses will be carried out in two stages. First, using intention-to-treat analysis and applying imputation data method for missing data. Then, using per-protocol analysis which consists of consider only participants without missing data for the primary endpoint. 

Categorical parameters will be described in terms of numbers and frequencies, whereas continuous variables will be expressed as mean and standard deviation or median and (inter-quartile range) according to statistical distribution. The assumption of normality will be studied using Shapiro–Wilk test. 

At inclusion, participants will be characterized and compared between groups according to the following variables: respect with eligibility criteria, epidemiological, clinical and treatment attributes. Using the characteristics of the participants and potential factors associated with the primary outcome, the comparability at baseline between groups will be assessed. According to both clinical and statistical considerations, a possible difference between the two groups on one of these characteristics will be determined. 

Intergroup comparisons will be systematically conducted (i) without adjustment and (ii) by adjusting for factors whose distribution could be unbalanced between groups. 

All statistical tests will be two-sided and *p* < 0.05 will be considered significant. Most of analyses of the secondary evaluation criteria will be exploratory. As discussed by Feise [39], the adjustment of the type I error will not be systematically proposed, but case by case in view of clinical considerations and not only statistical. 

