#### 3.3.1. Analyses for the Primary Outcome

To compare the primary endpoint between groups, we will use Student’s t-test, or the non-parametric Mann–Whitney test if assumptions of t-test are not met. 

For the primary analysis, the intention-to-treat analysis will be considered, i.e., the comparisons between groups (“intervention” group and “waiting list” group) between M1 and M3. To prevent attrition bias, imputation of the missing data is planned. Then, the analysis of the primary outcome will be completed by multivariable analysis using a linear mixed model to compare HRV parameters between randomized groups considering (i) covariates identified according to clinical relevance (such as sex, age, number of complete sessions performed, occupational characteristics) and univariate results and (ii) session as random effects (to measure the variability between and within session). We will study the normality of the residuals from linear regression. If needed, a logarithmic transformation of the dependent variable will be suggested. Effect sizes and 95% confidence intervals will be used to express result. 

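### The primary outcome is heart rate variability without a named parameter, so the 5% type I error is not secured among about 9 to 11 overlapping indices

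*Protocol article*

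**What the plan says.** - **Outcome.** Section 2.6: "The main outcome is heart rate variability change between M1 and M3". The matching row of Table 1 gives only heart rate variability and the device.
- **Indices.** Section 3.2.1: "Time and frequency domains will be used to explore HRV". It then lists time-domain and spectral quantities, with LF and HF also in normalized units, and Table 2 describes the components. Section 3.2.1 regards LFnu and HFnu as the best markers of sympathetic and parasympathetic activity but makes neither primary.
- **Effect size.** Section 3.1 expects that it "will be around 0.5 for HRV parameters".
- **Analysis.** Section 3.3.1 first plans a t-test or Mann–Whitney test of the primary endpoint, in the singular. It then completes this with a "linear mixed model to compare HRV parameters between randomized groups".
- **Significance.** The rule in Section 3.3 begins "All statistical tests will be two-sided and" and sets p < 0.05. The only text on multiplicity follows a sentence about secondary criteria and leaves adjustment to be decided case by case.
- **Secondary outcomes.** Sections 1 and 2.6 place other measures of autonomic activity among the secondary objectives and outcomes, without saying which measure they are other than.

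**The concern.** A confirmatory test needs one defined variable, or a defined set with a rule for combining the results. Here the singular wording implies one primary measure and the plural wording implies several, and neither is resolved. Someone following the text could test several indices at 5% each, or run one test on an index picked once the results are visible. Either way the primary claim no longer carries a 5% error rate.

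Direction is open as well. The aim is improved HRV, but the indices do not move together. Table 2 ties rMSSD, pNN50 and HF to parasympathetic activity and gives LF a sympathetic predominance. If more parasympathetic activity is what counts as improvement, HF and rMSSD should rise while LF/HF should fall. The article does not state this for any index, so what would count as success is not fixed.

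**Working it through.** **1. The stated sample size.** Inputs from Section 3.1: effect size d = 0.5, two-sided alpha 5%, power 90%, equal groups.

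n per group = 2(z₀.₉₇₅ + z₀.₉₀)² / d² = 2(1.960 + 1.282)² / 0.25 = 84.06, rounded up to 85.

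The exact t-test calculation gives 85.03, with power 0.900 at 85 per group. The 100 enrolled per group implies 15% loss: 85 / 0.85 = 100. The stated figures reproduce for one test of one index.

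**2. How many indices.** Table 2 has nine rows: RR, SDNN, rMSSD, pNN50, TP, LF, HF, LF/HF and VLF. Counting LF and HF in both ms² and normalized units gives 11. Section 3.2.1 does not list TP among the quantities to be analysed and describes VLF only in passing. Leaving those two out but counting both units again gives nine. So 11 is an upper count.

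**3. Overlap.** Section 3.2.1 defines normalized units as each band's share of total power minus VLF. If what remains is LF + HF, then LFnu + HFnu = 100 and LF/HF = LFnu / (100 − LFnu). A two-sided test of the change in LFnu is then the same test as for HFnu, and the ratio carries the same information. These three are not separate evidence.

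**4. Chance of at least one false positive, each index at two-sided 5%.** With independence it is 1 − 0.95^k. Otherwise it comes from simulating k equally correlated normal test statistics (400,000 draws). The correlations are assumptions; the documents give none.

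| Correlation | k = 4 (time domain only) | k = 9 | k = 11 |
|---|---|---|---|
| 0 (ceiling) | 18.5% | 37.0% | 43.1% |
| 0.3 | 17.4% | 32.6% | 37.6% |
| 0.5 | 15.7% | 26.9% | 30.4% |
| 0.7 | 12.9% | 20.3% | 22.2% |
| 0.9 | 9.4% | 12.4% | 13.1% |
| 0.95 | 8.0% | 9.8% | 10.3% |

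By step 3 the independence row cannot be reached for the 9 or 11 indices. Equal correlation does not capture the true structure either, so the rows show a range and are not an estimate. If every index were oriented so that higher is better and only favourable results counted, k = 11 would give 15.1% at 0.5, 11.1% at 0.7 and 5.1% at 0.95, against a nominal 2.5%.

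**5. Power if several indices were kept as primary.** With Bonferroni over 11, alpha = 0.05 / 11 = 0.00455 and z = 2.838.

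- Power per index at 85 per group = Φ(0.5 × √(85/2) − 2.838) = Φ(3.260 − 2.838) = 0.66 (0.65 by t-test).
- n for 90% power = 2(2.838 + 1.282)² / 0.25, rounded up to 136 evaluable per group (138 by t-test). With 15% loss, 136 / 0.85 = 160 enrolled.
- With nine indices: power 0.69 at 85 per group; 132 per group needed.

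**The case against.** Four arguments deserve weight.

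**The article does not say that all indices are co-primary.** This stands. A reader might infer a plan for 11 primary tests, but Section 3.3.1 names a single primary endpoint, the plural appears in the follow-up model and the effect-size sentence, Table 2 works largely as a glossary, and other autonomic measures are called secondary. The defect is an endpoint that is never identified. That does not make it harmless: choosing one index after seeing several results inflates the error in the same way as testing them all.

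**The power claim is sound.** This stands too. A reader might infer that the 90% power fails, but step 1 reproduces it for any one index at 5%. Power falls only if alpha is split or if every index must succeed, and the article plans neither.

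**The size is not established.** Largely true. The independence figure of 43% cannot occur given the overlap, and the true correlations are unknown. Still, every scenario in the table is above 5%.

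**The full protocol, the analysis plan or the registration may name the index, and Section 3.3 has analyses run before the randomization code is broken.** None of those documents is shown. An article does not commonly leave the identity of its primary variable to the analysis plan, because alpha, effect size and sample size rest on it, and Section 3.3 allows that plan to be revised during the study. Analysis under coded groups helps only if the index is chosen before the coded comparisons are run, since those already show which index reached p < 0.05.

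**Conclusion.** The point holds as a failure to designate the primary HRV parameter and its direction of improvement. As the article is written, the 5% type I error is guaranteed only if one index is fixed in advance. Testing or choosing among the described indices raises it, illustratively to about 30%, 22% or 10% for 11 indices at assumed equal correlations of 0.5, 0.7 or 0.95. These figures rest on the upper count of 11 and on correlations that are not in the documents. The case-by-case adjustment in Section 3.3 does not close the gap: it appears to concern secondary criteria and commits to no procedure. The sample size of 85 per group is correct for one pre-named index and needs no change on this account. The conclusion applies to the article as published; an unseen document may already name the parameter.

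**What to change.** Before unblinded data are seen, and before any HRV comparison by coded group is run:

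1. Name one HRV parameter as primary, with its unit and the direction that counts as improvement. The choice is the investigators'. Section 3.2.1 leans towards LFnu or HFnu; rMSSD is another option.
2. Keep the contrast as the change from M1 to M3 compared between groups.
3. Tie the 0.5 effect size in Section 3.1 to that parameter.
4. Make all other HRV indices secondary, and do not count LFnu, HFnu and LF/HF as separate evidence.
5. Use the same wording in Sections 2.6, 3.1 and 3.3.1, Table 1, the registration and the analysis plan.

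This costs wording only: no added participants, and every index can still be reported.

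If several indices are to stay primary, prespecify a multiplicity procedure and restate the power. With Bonferroni over 11, power per index at 85 per group is about 66%, and restoring 90% takes about 136 evaluable (160 enrolled) per group.

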## 3. Results

### 3.1. Justification of the Sample Size

This study aims to demonstrate an improved heart rate variability in the intervention group, in comparison with the control group. According to previous data [32], it seems reasonable to estimate that effect size, for the primary analysis between M1 and M3, will be around 0.5 for HRV parameters. Effect sizes are considered small between 0.20 and 0.50, moderate between 0.50 and 0.80, and high above 0.80 [33]. To highlight such clinically relevant difference, 85 participants per randomized group will be needed for a two-sided type I error at 5% (alpha level, i.e., showing a difference that does not exist), a statistical power at 90%. If the desired power level is typically 80%, we specified a higher power level of 90%, so there would be a 90% probability that we will not commit a type II error (beta-level, i.e., failing to show a real difference) [34,35]. Finally, it is proposed to include 100 patients per group to consider loss to follow-up.

### 3.2. Data Collection and Management

The material is presented in Table 1.

**Table 1 ijerph-20-01185-t001:** Synthesis of primary and secondary outcomes.

Variables	Type of Measures	Modalities to Measure	Time of Measures		References
			Group Intervention	Group “Waiting List”	
Autonomic nervous system	Heart rate variability	Zephyr™ BioHarness™ BT	**Intervention**: 1 during each sophrology sessions (6 to 8 sessions) **Rest of the time**: 1 by month		[36]
	Skin conductance	Wristband electrodes—Empatica E4, Milano, Italy	**Intervention**: 1 during each sophrology sessions (6 to 8 sessions) **Rest of the time**: 1 by month		[37]
Demographic *	Age, gender, marital status, children, occupation, and recent stressful event	Questionnaire	**Age, gender and recent stressful event**: once at inclusion then every week **Marital status, children and occupation**: once at inclusion		[36]
Clinical measurements	Height, weight	Questionnaire	**Height**: once at inclusion **Weight**: 5 times (M0, M1, M3, M5 and M7)		[38]
Psychology and quality of life	Depression	HAD 7 items	**5 times**: M0, M1, M3, M5 and M7		[39]
	Anxiety	HAD 7 items			[39]
	Burn-out	Maslach Burn-Out Inventory			[40]
	Perception of work	Job Content Questionnaire of Karasek			[27]
		Effort Reward Imbalance			[41,42,43]
	Alexithymia	Toronto Alexithymia Scale (TAS-20)			[44,45,46,47,48]
	Stress at home, fatigue, sleep quality, anxiety, mood, family support, stress at work, burnout, job control, job demand, hierarchy support, colleagues support, effort reward imbalance	Visual analog scale of 100 mm	1 by week during the whole protocol		[36]
Lifestyle	Coffee/tea, food intakes	Questionnaire	**Coffee/tea**: once by week during the whole protocol **Food intakes**: 5 times (M0, M1, M3, M5 and M7)		[11]
	Physical activity	Recent Physical Activity Questionnaire (RPAQ)	5 times (M0, M1, M3, M5 and M7)		[49]
		Questionnaire	1 by week during the whole protocol		
	Consumption of alcohol, tobacco, cannabis and medication	Questionnaire	**Alcohol, tobacco and cannabis**: every week **Medication**: 5 times (M0, M1, M3, M5 and M7)		[7]
Sophrology practice	Number of sessions per week	Questionnaire	1 by week during the whole protocol		
	Stress before and after the last sophrology session	Visual analog scale of 100 mm	1 by week during the whole protocol		[7]
Allostatic load **	Cortisol	Saliva sampling and deep-freezing	**Intervention**: 1 during each sophrology sessions (6 to 8 sessions) **Rest of the time**: 1 by month		[23,24,25] (1, 2)
	DHEAS	Saliva sampling and deep-freezing			[23,24,26]
	Leptin	Saliva sampling and deep-freezing			[27,28]
	Ghrelin	Saliva sampling and deep-freezing			[28,29,30,31]

* Adjustment variables; ** Saliva samples upon waking up to control the circadian rhythm of biomarkers.

